A further group of rehabilitation strategies for brain-lesioned patients, including DOC patients, consists of neuromodulation aimed to alter the physiology of the neural circuits responsible for the behaviour under investigation. Among several neuromodulation approaches, there are pharmacological interventions (e.g., amantadine hydrochloride) [29], deep brain stimulation (for a review see [30]), and Non-Invasive Brain Stimulation techniques (NIBS) [31]. NIBS exists in various forms, although one of the most adopted in clinical settings is transcranial electrical stimulation (tES). This technique consists of delivering a small (1–2 mA) current via two electrodes placed on the scalp. According to the stimulation parameters, tES affects neural excitability and has plastic effects (mediated by NMDA-receptors) [32]. These currents, cathodal (-) or anodal (+), generate an electric field that can modulate spontaneous neural activity by interfering with the membrane potential of the underlying neuronal compartments by inducing, respectively, hyperpolarization (inhibiting effect) or depolarization (facilitating effect) [33]. Importantly, the induced changes become more stable and long-lasting (i.e., aftereffects) when stimulation is repeated several times [34]. Key targets for stimulation in the neurocognitive domain are the dorsolateral prefrontal cortex (DLPFC), especially in working memory, attention, and executive functions, and the posterior parietal cortex (PPC), which plays a critical role in visual spatial perception and attentional processes [35]. Several tES studies show improvements in clinical (e.g., GCS, CRS-R, cognitive, motor) and surrogate (i.e., EEG, TMS, fMRI) outcomes of patients with DOC [36–38], for a review see Kuo et al. [39], although this effect is more evident among MCS patients rather than among unresponsive wakefulness syndrome patients (VS/UWS) [40]. NIBS is, thus, considered a useful tool in the rehabilitation of clinical populations such as patients with DOC [41]; for instance, tES has been used as a potential adjuvant treatment to improve symptoms in patients with hemispatial neglect after stroke [42]. However, there is an increasing understanding that patients do not homogeneously respond to NIBS]. This might be ascribed to the fact that the methodology adopted in tES studies is characterised by a large variability as concerns stimulation parameters, participant characteristics as well as the characteristics of associated rehabilitation treatment.

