### Sample size determination

The effect size to be expected is uncertain as no study so far has implemented a combined intervention of music and electrical stimulation in DOC patients. We assume it to be in the medium-to large range (i.e., Cohen’s d between 0.5 and 0.8). We aim to achieve 80% power (*f* = 0.30) in a repeated-measures analysis of variance (*a* = 0.05, power (1-b) = 0.80) with condition as between-subject factor (tES combined with music stimulation vs. sham stimulation, and noise vs. music stimulation and sham stimulation), and time (pre-intervention, post-intervention and post-placebo), as within-subject factor. Power calculations (using G* Power 3) indicate that a valid sample size of *n* = 10 per group will result in 80% statistical power if the effect is *d* = 0.68, which is in the medium-to-large range. This results in a total sample size of *n* = 30.

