### Experimental design and procedures

The experimental paradigm is one of the main strengths of the study, as a randomized cross-over design will be used in this trial, including a treatment condition with electric brain stimulation combined with music listening and a placebo condition with sham brain stimulation combined with noise listening. The randomization of the participants to be included in each group will be done using the software “Research Randomizer” (www.randomizer.org). The randomization procedure will be performed by an independent researcher unrelated to the study. The randomization file will be saved in a password-protected online database. This independent researcher will enrol participants and will assign the patients to intervention groups. Both patients and examiner will be fully blinded.

Assessment times of outcome measures will be conducted at admission (T_0_), after the first weeks of post-intervention or post-placebo (T_1_), and after the second two weeks of post-intervention or post-placebo (T_2_) (Fig 1). Patients will be randomized into three groups depending on the order of the stimulation or placebo conditions:

Stimulation-Placebo: Patients receiving tES combined with music stimulation for 2 weeks, 1 week of wash out, then sham stimulation combined with noise (placebo) for other 2 weeks.Placebo-stimulation (combined tES and music): Patients receiving sham stimulation and noise (placebo) for the first 2 weeks, then 1 week wash out, and finally tES and music stimulation for other 2 weeks.Music-placebo: Patients receiving music stimulation and sham stimulation for 2 weeks, 1 week of wash out, then sham stimulation and noise (placebo) for another 2 weeks.

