### Data analysis

The SPSS 23.0 statistical software will be used for the data analysis. All the statistical hypotheses will be tested by two-side test, with statistically significant test level set at 0.05 and the confidence interval estimation to 95%.

The aim of our study is to evaluate the effects of the treatments in the various patient groups on the primary and secondary outcomes. Descriptive analysis of the data will allow us to identify the characteristics of the groups. Comparison of demographic and clinical characteristics of the groups will be performed using one-way ANOVA for continuous variables and the Chi-square test for categorical variables. Considering the crossover and longitudinal aspects, primary analyses will focus on behavioural changes at group level, comparing the treatments. Moreover, at the individual level, we will analyse the differences between pre-treatments and post treatments data.

As for the primary outcomes, we will measure the effects of the intervention on the following measures (two neurophysiological and two clinical and behavioral): (i) power spectra of frequency band extracted from the EEG recordings; (ii) auditory evoked responses, extracted from the EEG recordings; (iii) behavioural responses of DOC patients, measured through CRS-R.

Baseline characteristics and carryover effect will be analysed between the three sequences using ANOVA and chi-square test. By including the order of intervention as a covariate, we aim to determine whether the sequence in which participants receive the interventions impacts the observed outcomes. To assess the presence and magnitude of the washout effect, we plan to incorporate appropriate statistical methods into our analysis, such as comparing outcomes during the washout period to those observed during active treatment phases. To this end, we will use repeated measures ANOVA considering time (before, during, and after the washout) as the independent variable, with behavioral measurements as the dependent variables.

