To reach the goal of obtaining the above-described neurophysiological outcome measures, we will first pre-process the EEG data as follows. Data will be filtered to remove low frequencies not originating from the brain and to control for interference of the electric current, by means of a generic FIR filter, set up as a bandpass filter, with low cut-off at 0.5 Hz and high cut-off at 45 Hz (because of 50 Hz power line noise). Cerebral signals contaminated by artifacts will be identified and removed. Moreover, independent component analysis (ICA) will be performed. ICA algorithms will be used to detect and isolate artifacts, such as eye blinks, eye saccades, hearth, muscle, line noise, channel noise and others. In this way, the original signal will be decomposed into independent components: we will individuate and discard the components that picked up the artifacts activities and reconstruct a clear signal by using only the remaining components [70]. Further pre-processing steps will include epoch extraction, baseline removal, resampling, re-referencing to low temporal electrodes, and filtering.

To investigate whether slow neural oscillations are reduced and fast neural oscillations are increased post-treatment, the continuous EEG will first be divided into 2-seconds segments, transformed into the frequency domain with fast Fourier transform, inspected for myogenic artifact segments that will be rejected, and then averaged across the segments [71]. Any further exploratory analyses will be specified in the future publication of the findings of this study. Missing data will be treated according to Molenberghs et al. [72].

We will evaluate the music and electrical intervention effects on power spectra of frequency bands measuring EEG at rest and during music listening at T0 (pre-intervention), T1 (post-intervention) and T2 (post-placebo). To this end, we will compare the power spectra between rest and music conditions and across time. The ratio of fast (8–30 Hz, alpha and beta) to slow (2–8 Hz, delta and theta) oscillation amplitude at the midline electrodes (Fz, Cz, Pz, Oz) will be measured [70] and compared pre- and post- intervention using t-tests with cluster-based corrections of the multiple comparison problem. In the case of non-normal distributions, there will be applied mixed-effect ANOVAs or non-parametric equivalents to the parametric tests.

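### The planned washout ANOVA cannot be run on the T0/T1/T2 schedule, which leaves only a weak between-sequence check of carryover

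*Protocol article*

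**What the plan says.** The Data analysis section plans to assess the presence and size of a washout effect by "comparing outcomes during the washout period to those observed during active treatment phases". The stated method is: "we will use repeated measures ANOVA considering time (before, during, and after the washout) as the independent variable". The dependent variables are the behavioural measurements. The same section separately plans an ANOVA of carryover between the three sequences and an order-of-intervention covariate.

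Experimental design and procedures fixes the assessments: "Assessment times of outcome measures will be conducted at admission (T_0_), after the first weeks of post-intervention or post-placebo (T_1"), then "after the second two weeks of post-intervention or post-placebo (T_2"). The washout is one week between two 2-week periods. The three sequences are Stimulation-Placebo, Placebo-Stimulation and Music-placebo.

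Two other places use three times as well. The EEG plan speaks of "measuring EEG at rest and during music listening at T0 (pre-intervention), T1 (post-intervention) and T2 (post-placebo"), and the sample size model uses "time (pre-intervention, post-intervention and post-placebo), as within-subject factor".

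On persistence, the Introduction states that "the induced changes become more stable and long-lasting (i.e., aftereffects) when stimulation is repeated several times".

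**The concern.** The washout ANOVA needs three time levels, one of them inside the washout and one at its end. The listed visits supply neither, and period 2 has no baseline of its own.

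The washout is the assumption on which the second period depends. The intervention is meant to produce lasting change, and one week is allowed for it to fade. Two of the three sequences give active treatment first, so any residue falls into their placebo period and makes placebo look more like treatment at T2. An analysis that cannot be carried out leaves this assumption without the check that the plan promises.

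**Working it through.** **Step 1: schedule against analysis.** Reading T1 as the end of the first 2-week period:

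| Point | Week | Outcome measured? |
|---|---|---|
| T0, admission | 0 | yes |
| T1, end of period 1 | end of 2 | yes |
| During washout | 3 | no |
| End of washout, before period 2 | end of 3 | no |
| T2, end of period 2 | end of 5 | yes |

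- Before washout: available, as T1.
- During washout: no measurement.
- After washout: the only later value is T2, which mixes any washout effect with two weeks of the second condition.

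If T1 were instead read as falling after the washout, the level before washout would be lost. The ANOVA cannot be run under either reading.

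**Step 2: what the remaining check can detect.** The between-sequence comparison needs only T1 and T2. The plan gives no power for it, so there is no stated figure to reproduce.

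Inputs from the protocol: 10 patients per sequence and d = 0.68 (Sample size determination); two-sided 0.05 (Data analysis). Assumed, because the document gives none: equal unit variances at T1 and T2, and a within-patient correlation ρ of 0.3 to 0.9.

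Compare T1+T2 totals in Stimulation-Placebo and Placebo-Stimulation. If a share c of the effect persists to T2, the expected totals are d + c·d and d, so the difference is c·d.

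- SD of a total = √(2(1+ρ))
- SE of the difference = SD × √(2/10)
- Noncentrality = c·d / SE, with 18 df

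At ρ = 0.5: SD = √3 = 1.732, SE = 1.732 × 0.447 = 0.775, and for c = 1 the noncentrality is 0.68/0.775 = 0.88.

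| ρ | Power, c = 0.5 (0.34 SD) | Power, c = 1 (0.68 SD) |
|---|---|---|
| 0.3 | 7.3% | 14.5% |
| 0.5 | 7.0% | 13.2% |
| 0.7 | 6.8% | 12.2% |
| 0.9 | 6.6% | 11.5% |

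Adjusting the totals for T0 changes the SD to √(2(1+ρ) − 4ρ²). For c = 1, power becomes about 18%, 22% and 49% at ρ = 0.5, 0.7 and 0.9.

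**Step 3: the music sequence.** The comparison in step 2 uses two mirrored orders. Music-placebo has no placebo-music counterpart, so music carryover cannot be separated from period effects or spontaneous recovery.

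**Step 4: a comparison free of carryover.** The randomised T1 contrast of combined treatment against placebo, 10 vs 10, cannot be affected by carryover. Adjusted for T0 at ρ = 0.5, the residual SD is √(1 − 0.25) = 0.866, the SE is 0.866 × 0.447 = 0.387, and the noncentrality is 0.68/0.387 = 1.76. Power is about 38%, against 30% unadjusted.

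**The case against.** A reader might infer that carryover cannot be checked at all. The protocol does not support that: the between-sequence ANOVA and the order covariate can be run on T1 and T2. They are weak, but they exist, and with T0 adjustment and a very high correlation power approaches one half.

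A reader might also want to put a figure on the loss to the treatment contrast. A 20-patient paired crossover contrast with d = 0.68 and ρ = 0.5 would fall from 82% power to 58% if half the effect persisted, and to 30% if all of it did. At ρ = 0.7 the figures are 96%, 80% and 46%. The protocol does not specify that contrast; it powers a group-by-time repeated-measures ANOVA. These figures illustrate the direction of the harm and do not measure it for this plan.

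Nor does the text say that the periods will be pooled after a non-significant carryover test. That misuse is a risk to rule out, not something the plan commits.

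The evidence on the schedule also has a limit. The washout ANOVA concerns behavioural measures, whereas the EEG list and the sample size model concern other things, so the behavioural schedule rests mainly on Experimental design and procedures. Figure 1 is not shown and could contain a further visit. This does not remove the point: that section states the assessment times for outcome measures and lists none in the washout.

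Finally, the washout ANOVA is a diagnostic and not the main treatment comparison. That limits its weight, but the protocol still commits to an analysis that its listed visits cannot supply.

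**Conclusion.** The concern holds in this form: the washout ANOVA and the assessment schedule contradict each other, and the analysis cannot be run as written. Only one of its three time levels is available cleanly.

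The remaining between-sequence test would miss a full 0.68 SD carryover in roughly 85–88% of trials on unadjusted totals, for assumed correlations of 0.3 to 0.9, and it says nothing separate about music. A non-significant result would therefore not be evidence that the one-week washout was sufficient.

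The contradiction rests on the text alone. The power figures rest on the assumed correlation, equal variances and the protocol's own d = 0.68. The conclusion would change only if a washout assessment exists that the text does not list.

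**What to change.** **Preferred.** Score the CRS-R once more at the end of the washout week, before period 2, and list this visit in Experimental design and procedures. Restate the washout analysis as T1 versus end of washout, by sequence. Drop the level during washout, and use the new score as the period-2 baseline. The cost is one bedside assessment per patient, 30 in all, by staff who already score the scale, plus an ethics amendment. If Figure 1 or the full protocol already has such a visit, only the text needs correcting.

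**If no assessment is added.** Delete the washout ANOVA and the claim that it will show the presence and magnitude of a washout effect. State that a non-significant between-sequence test is not evidence of no carryover. Report the randomised, T0-adjusted T1 comparison as a sensitivity analysis free of carryover. It need not become primary: at about 38% power (d = 0.68, 10 vs 10, ρ = 0.5) that would trade precision for freedom from this bias, and the choice should be made openly. This route costs only wording, but the washout assumption then stays essentially untested.

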
With this study we propose a novel rehabilitation protocol that combines music-based intervention and NIBS in neurological patients aimed to (i) assess the residual neuroplastic processes existing in DOC state, and (ii) evaluate the putative modulation of these processes by a non-pharmacological 2-weeks intervention combining electric (tES) and auditory (music) stimulation. The musical stimulation will consist of musical pieces that vary in familiarity and complexity (from pieces chosen from the favourite ones for the patient to novel pieces following classical tonal style up to atonal pieces). We hypothesize that tES, altering the physiology of neural circuits, can increase the plastic effect of music stimulation and thus increase the responsiveness of the patient. As far as we know, there are no studies in the literature that have evaluated the effectiveness of the association of these treatments in DOC patients Furthermore, an additional novel aspect will be the use of autobiographical music, hence emotionally relevant to the patients.

In addition, we also want to ascertain the influence of this rehabilitation protocol on caregiver’s burden and psychological distress, since acquired brain injury has an important impact on physical, psychological, social and also financial conditions of caregivers; their entire life is modified in order to take care of the patient, causing a strong emotional burden, with high levels of psychophysiological distress, depression, anxiety and a more complex symptomatology called prolonged grief disorders [43, 44]. In this regard, an aim of this study is to evaluate the caregiver’s psychological burden both before and post rehabilitation treatment in order to assess the effect of music stimulation and brain stimulation also on caregiver’s emotional condition.

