For the secondary outcome we will measure the effects of the treatments on caregivers’ depression, anxiety, psychophysiological symptoms, grief, strain and quality of life in order to evaluate the effectiveness in reducing the caregiver’s burden and psychological distress. Repeated-measures analysis of variance, as well as post-hoc paired *t*-tests will be conducted to assess the effects of the treatments over time on N1, P1, and P2 amplitudes and latencies, as well as level of consciousness. All these primary outcome variables will be analysed separately, using parametric or non-parametric tests for continuous and categorical variables respectively.

For the behavioural outcome, we expect an improvement of level of consciousness, as measured by CRS-R.

For the caregiver’s burden, we expect a positive effect of this new treatment protocol on caregiver’s wellbeing, with a decrease of psychological distress.

For neurophysiological outcome measures, we expect to obtain in DOC patients an increased EEG power spectrum in slow frequency bands, following a previous study [67] showing a generalized slowing in the theta or delta range associated with a significantly diminished α power. Power spectrum analysis is one of the standard methods used for quantification of the EEG. The power spectrum, namely the power spectral density, reflects the ‘frequency content’ of the signal or the distribution of signal power over frequency [68].

For the computation of the auditory evoked responses, the average EEG will be measured time-locked to the sound onset events in the music stimuli, after rejecting any residual noise exceeding 100 μV. P1 (fronto-central positive potential with ~50 ms latency), N1 (fronto-central negative potential with ~100 ms latency), and P2 (fronto-central positive potential with ~200 ms latency) amplitudes and latencies will be measured at the Fz and Cz electrodes [69], and compared pre- and post- intervention.

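### No named analysis isolates whether tES adds to music: the three-group ANOVA is not specific to that question, and paired t-tests cannot compare two separate groups

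*Protocol article*

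**What the plan says.** - **Hypothesis** (Introduction, aims): "We hypothesize that tES, altering the physiology of neural circuits, can increase the plastic effect of music stimulation". The matching null is that combined treatment equals music alone.
- **Sequences** (Experimental design and procedures): combined then placebo; placebo then combined; music with sham then placebo. T1 and T2 are calendar visits, each following either active treatment or placebo according to sequence.
- **Planned model** (Sample size determination): "We aim to achieve 80% power (*f* = 0.30) in a repeated-measures analysis of variance", with a three-level condition factor between patients and a three-level time factor within patients. Here the time levels are labelled by condition: baseline, after active treatment, after placebo.
- **Follow-up tests** (Data analysis): "Repeated-measures analysis of variance, as well as post-hoc paired *t*-tests will be conducted to assess the effects of the treatments over time", covering evoked responses and level of consciousness. The fast-to-slow EEG ratio gets cluster-corrected pre/post t-tests, with mixed-effect ANOVAs or non-parametric equivalents as fallback.
- **General statement** (Data analysis): the primary analyses compare treatments at group level, without naming a contrast. The EEG text there fixes T1 as post-intervention and T2 as post-placebo.

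**The concern.** Only a comparison between the Stimulation-Placebo and Music-Placebo groups can show what tES adds, because no patient receives both conditions. The plan names no such comparison. It names an omnibus test, whose interaction null is that all three profiles over time are parallel, and within-patient tests, whose null is no change within a group.

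The profiles can fail to be parallel for reasons unrelated to tES. The placebo-first group may be on the other treatment at the same visit, effects may persist past the one-week washout, or patients may recover spontaneously. Likewise, a significant change in the combined arm beside a non-significant change in the music arm is not a comparison of the two arms. Either result could be taken as support for the combination without being evidence for it.

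**Working it through.** **Inputs from the document.** 10 per group, N = 30; effect 0.68 SD ("will result in 80% statistical power if the effect is *d* = 0.68"), within the allowed range "Cohen’s d between 0.5 and 0.8"; tests two-sided, "with statistically significant test level set at 0.05". Sequences are those in Experimental design and procedures. The Abstract also lists a tES-only arm, which those sequences do not contain.

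**Assumed, because not stated.** SD 1; equal correlation ρ between visits, 0.3 to 0.7; carryover from none to full; where shown, spontaneous recovery of 0.5 SD per visit.

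**The plan's own figure.** For k groups and m times, λ = f²·N·m/(1−ρ), with (k−1)(m−1) and (N−k)(m−1) df. With f = 0.30, k = 3, m = 2 and ρ = 0.5, λ = 0.09·30·2/0.5 = 10.8 and power is 0.80. With the stated m = 3, λ = 16.2 and power is 0.89 at ρ = 0.5; it is 0.745 at ρ = 0.3. So 80% is reproducible with unstated choices, but it refers to the omnibus interaction.

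**Interaction when tES adds nothing.** λ = n·(sum of squared interaction deviations)/(1−ρ), on 4 and 54 df. When the placebo-first group differs from two identical groups by a profile δ, that sum is (2/3) times the sum of squares of δ about its own mean. With d = 0.68, d² = 0.4624:

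1. *Calendar coding, no carryover.* Profiles (0,d,0), (0,0,d), (0,d,0); δ = (0,−d,d); sum = (4/3)d². At ρ = 0.5, λ = 10·(4/3)·0.4624/0.5 = 12.33.
2. *Calendar coding, full carryover.* Profiles (0,d,d), (0,0,d), (0,d,d); δ = (0,−d,0); sum = (4/9)d²; λ = 4.11 at ρ = 0.5.
3. *Condition coding, no carryover or period effect.* All profiles are (0,d,0), so λ = 0.
4. *Condition coding, full carryover.* δ = (0,0,−d); sum = (4/9)d², the same as case 2.
5. *Condition coding, recovery 0.5 SD per visit.* δ = (0,0.5,−0.5); sum = (2/3)·0.5 = 1/3; λ = 10/(3·0.5) = 6.67 at ρ = 0.5.

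| Probability of a significant interaction, tES adding nothing | ρ = 0.3 | ρ = 0.5 | ρ = 0.7 |
|---|---|---|---|
| Calendar, no carryover | 0.61 | 0.77 | 0.95 |
| Calendar, full carryover | 0.22 | 0.30 | 0.49 |
| Condition, no carryover or period effect | 0.05 | 0.05 | 0.05 |
| Condition, full carryover | 0.22 | 0.30 | 0.49 |
| Condition, recovery 0.5 SD per visit | 0.35 | 0.48 | 0.72 |

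A simulation of 20,000 trials gave 0.769 for the calendar, no-carryover case at ρ = 0.5.

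**Can the interaction discriminate?** Suppose instead that music does nothing and tES carries the whole 0.68 SD, with ρ = 0.5 and no carryover. Under calendar coding the interaction is then significant in about 0.68 of trials, less often than the 0.77 when tES adds nothing. Under condition coding it is significant in 0.30, which is also the rate when tES adds nothing but effects persist fully.

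**Paired tests.** The standardised change is d/√(2(1−ρ)): 0.57, 0.68 and 0.88 at ρ = 0.3, 0.5 and 0.7. With n = 10, power p is 0.37, 0.48 and 0.70. If both arms have the same true effect, they disagree with probability 2p(1−p): 0.47, 0.50 and 0.42. Half of these disagreements (about 25% of trials at ρ = 0.5) show the combined arm significant and the music arm not.

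**Direct contrast, 10 versus 10 at T1, adjusted for T0.** It rejects in about 5% of trials when tES adds nothing. Power at 0.68 SD is about 36% to 38% at ρ = 0.5 and 50% to 52% at ρ = 0.7, depending on whether it is simulated or approximated. On unadjusted change scores at ρ = 0.5 it is 30%.

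**The case against.** The strongest objection concerns time coding. Sample size determination labels the time levels by condition, and under that coding, without carryover or period effects, the interaction holds its 5% level when tES adds nothing and has about 30% power (ρ = 0.5) when tES carries the whole effect. This stands, and it rules out a flat claim that the ANOVA is significant about 77% of the time when tES is useless. That figure needs calendar coding, ρ = 0.5, no carryover and the interaction being the term read. Nor is it a type I error of the ANOVA, since the profiles really do differ in that case. The article does not say which ANOVA term will be read, and the group main effect rejects only about 5% in that same case.

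Three further limits also stand. The hypothesis is not designated the main one; the Abstract lists three main objectives. The ANOVA and paired t-tests are not the only tests named. And nothing says that a significant omnibus result will be reported as proof that tES adds to music; a reader might infer this, but the text does not state it.

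The objection that the contrast is detail for a fuller plan stands only in part. The article itself chose the follow-up tests, and paired t-tests cannot compare two separate groups. Condition coding does not rescue the interaction either, once carryover or recovery is allowed.

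**Conclusion.** The concern holds in a conditional form. The hypothesis that tES increases the effect of music has no named test that isolates it. The named within-patient tests cannot supply one, and the interaction is specific to it only under condition coding with no carryover and no period effect.

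With tES adding nothing, the interaction is significant in 5% to 95% of trials across the cases tabulated. Where it lies depends on the time coding, on which the article is inconsistent, and on correlation, carryover and recovery, which the article does not quantify. The disagreement rate of 42% to 50% for the paired tests assumes a common effect of 0.68 SD and 10 patients per arm, but does not depend on the time coding. The stated 80% power does not apply to this question.

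**What to change.** 1. For the hypothesis in the Introduction, name one between-group contrast: CRS-R at T1, Stimulation-Placebo versus Music-Placebo, adjusted for T0 by ANCOVA, reported with its 95% CI. A contrast that also uses the second period could be defended, but it would rest on assumptions about carryover and period effects.
2. Reconcile the meaning of T1 and T2 across Sample size determination, Experimental design and procedures, and Data analysis. Fixing T1 as post-intervention is untrue for the placebo-first sequence.
3. State that the omnibus test and the within-group paired t-tests are not evidence that tES adds to music.
4. State the power of the contrast: about 36% at correlation 0.5 and 50% at 0.7 for 0.68 SD.

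The cost is analysis wording only, with no new data. The price is admitting that 10 per arm leaves this question underpowered. On change scores at correlation 0.5, 80% power for 0.68 SD would need about 35 per arm.
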